### 8.2.6 Safety evaluation

The full-analysis set will be used to address issues of safety. Adverse events data will be processed in the statistical analysis after coding according to the MedDRA dictionary.

Adverse events (AEs) will be classified as pre-treatment AEs or treatment-emergent AEs. Analyses will be performed for these classes. Pre-treatment AEs are defined to be AEs, which obviously occurred prior to the first administration of study medication. Treatment-emergent AEs are defined to be AEs, which occurred at or after the first administration of study medication. In case of doubt regarding the timing of AE onset the worst-case scenario will be applied, i.e. the AE will be considered as treatment-emergent.

AEs will be analysed regarding their seriousness, severity, outcome and causality assessment. SAEs will be analysed regarding their severity, outcome and causality assessment. Furthermore, all AEs with possible, probable or definite causal relationship to study medication (causality assessment) will be summarised as 'drug-related' AEs. They will be analysed regarding severity and outcome. All analyses will report frequency counts of subjects by MedDRA SOC and preferred term. Furthermore, treatment-emergent AEs will be presented by preferred term and sorted by frequency.

Listings by subject will be provided for SAEs and for AEs.

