## 7 ADVERSE EVENTS

### 7.1 Definitions

#### 7.1.1 Adverse event (AE)

The term adverse event describes any untoward medical occurrence in a patient or a clinical investigation subject, which does not necessarily have a causal relationship with the study treatment.

This definition includes:

- Any sign or symptom occurring during the study
- Any event or disease present on the day of inclusion in the trial with symptoms that worsen during the study
- Any accident
- Any significant change in laboratory parameters
- Any reaction to drug withdrawal
- Any drug interaction
- Any effect related to overdose, abuse or dependence

This definition also applies to events occurring in any comparative group (active treatment or placebo) or during the placebo-treatment phase or during periods when the patient is not receiving any study medication.

Note: the term study treatment refers to all the drugs studied including the reference drugs and any other treatment stipulated in the protocol.

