## **7.2 Monitoring and recording of adverse events**

At each visit after V0 the investigator must question the patient about the occurrence of any adverse event and note any abnormal laboratory findings. A neutral question such as "since the last visit have you felt any untoward or unusual symptoms other than those related to your illness?" elicits any adverse events experienced by the patient.

Whatever the relation to the study treatment is, any adverse event such as those described in section 7.1 spontaneously reported by the patient or observed by the investigator must be reported on the appropriate page of the case report form. For each adverse event, the following information should be documented:

- Description of the event (diagnosis and symptoms in verbatim terms)
- Outcome
- Seriousness
- Duration (start date and stop date)
- Severity (mild, moderate or severe); see section 7.1.4
- Frequency (permanent, intermittent)
- Causal relationship with the study treatment according to the scale shown in section 7.3
- Corrective actions including measures taken for the study treatment

The study number, patient number and investigator's signature must also be noted.

Any clinically significant event including any abnormal laboratory result or vital sign must be followed-up until it has completely disappeared or the investigator has assessed its sequelae, even after the end of the study.

The results of any complementary tests performed (laboratory tests, ECG, X-rays etc.) must be dated and appended to the CRF. The investigator must evaluate each adverse event and give his/her opinion about the causal relationship with the drug(s) used.

A period of 14 days for follow up of AEs after the patient has routinely or prematurely terminated the study seems sufficient.

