## **7.6 Premature discontinuation / Patient replacement**

Each patient can at any time withdraw from the study without personal disadvantages and without stating reasons.

Whenever possible, all patients prematurely discontinuing study medication will continue to be followed and complete all scheduled evaluations for the duration of the study. The reason(s) for premature cessation of a patient's participation during the trial, other than death, should be specified on the case report form. Whenever possible the evaluations scheduled for the end of the treatment period should be performed.

Study treatment may be stopped prematurely if any of the following events occur, according to the judgement of the investigator:

- Significant intolerance of the study medication, or significant clinical or laboratory findings, e.g. increase in ASAT or ALAT >2.5 upper limit of normal
- Significant intercurrent illness or emergency situation requiring cessation of the study
- The patient wishes to terminate his/her participation in the study
- Investigator judgement that it is in the best interest of the patient
- Failure to comply with the investigational procedures
- Pregnancy
- Technical reasons (change of physician, change of address of volunteer/patient)

Patients who have started double-blind treatment will not be replaced.

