### HISTORY RELEVANT TO THE SAE: medical, social, family and drug history etc.

### TIMING OF THE SAE: (When did the SAE occur?)

- ☐ Before treatment with study medication
 ☐ During treatment
 ☐ During follow-up (after stopping study medication)

|                              |               |                   |  |               |
|------------------------------|---------------|-------------------|--|---------------|
| Trial No.
GERP ALS | Screening No. | Randomisation No. |  | Investigator: |
|------------------------------|---------------|-------------------|--|---------------|

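### Section 8.2.6 gives treatment-emergent adverse events a start but no end, so events long after the last dose count; the effect is small and an added on-treatment table cures it

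*Protocol*

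**What the plan says.** Section 8.2.6 of the protocol sets the classes: "Adverse events (AEs) will be classified as pre-treatment AEs or treatment-emergent AEs". The second class is then defined: "Treatment-emergent AEs are defined to be AEs, which occurred at or after the first administration of study medication". If the timing is in doubt, the event goes to the treatment-emergent class. The tables are counts of subjects in the full-analysis set, by MedDRA class and term. A separate summary covers events that the investigator judged possibly, probably or definitely related to the drug.

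Three other sections decide what falls into the second class:

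- **Section 7.1.1** counts as adverse events those that arise "during periods when the patient is not receiving any study medication".
- **Section 7.2** has patients asked about adverse events at every visit after screening. It sets the end of collection as follows: "A period of 14 days for follow up of AEs after the patient has routinely or prematurely terminated the study seems sufficient".
- **Section 7.6** governs patients who stop the drug: "Whenever possible, all patients prematurely discontinuing study medication will continue to be followed and complete all scheduled evaluations for the duration of the study".

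The SAE form in Appendix V has three timing boxes: before treatment, during treatment, and in follow-up after treatment has stopped.

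**The concern.** Read together, these sections make the treatment-emergent class open-ended for one group: patients who stop the drug but stay in follow-up. Someone who stops at month 2 and has an infection at month 15 is a treatment-emergent case in the assigned arm, 13 months off drug.

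Such events occur at the background rate in both arms. They pull the ratio for a drug-caused event towards 1 and raise the reported incidence. More stopping means more dilution. Safety and tolerability are stated objectives (section 3), and the treatment-emergent tables are their main display.

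A related weakness is that the tables are subject counts without exposure. If the drug prolongs survival as planned, the test arm is observed for longer and collects more events for that reason alone.

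**Working it through.** **No stated figure is in dispute.** The defect lies in a definition, so the calculation only sizes its effect.

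**Step 1: reach of the rule.** The 14 days in section 7.2 run from leaving the study, and the two weeks for SAEs in section 7.4.1 run from the end of the study. For completers, and for patients who leave the study when they stop the drug, off-drug events are therefore limited to about 14 days. For patients who stop the drug and remain in follow-up, neither limit applies until they leave the study. Late events arise only in that group.

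**Step 2: inputs.**
- From section 8.1: 18-month survival S of 60% (standard) and 78% (test).
- Assumed, because the protocol gives no rate: a share p of 10%, 20% or 30% stops the drug by month 18, at a constant hazard equal in both arms.
- Assumed: every stopper is followed to death or month 18; on-treatment time ends w = 14 days (0.46 month) after the last dose; the background event rate is 1% per month, doubled during on-treatment time in the test arm.

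**Step 3: off-drug share of observation time.**
- Death hazard m = −ln(S)/18: 0.0284 (placebo) and 0.0138 (test) per month.
- Stopping hazard s = −ln(1 − p)/18: 0.00585, 0.01240 and 0.01981 per month.
- Mean observed time O = (1 − S)/m: 0.40/0.02838 = 14.095 months (placebo) and 0.22/0.01380 = 15.938 months (test).
- Mean on-treatment time A = (1 − e^(−mw))/m + e^(−mw) × [1 − e^(−(m+s)(18−w))]/(m+s).
- Off-drug share f = 1 − A/O. The rate ratio when all time after first dose is counted is 2(1 − f) + f = 2 − f, with f from the test arm.

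| Stopped by month 18 | A placebo | f placebo | A test | f test | Rate ratio, true value 2 |
|---|---|---|---|---|---|
| 10% | 13.473 | 4.4% | 15.200 | 4.6% | 1.95 |
| 20% | 12.824 | 9.0% | 14.432 | 9.4% | 1.91 |
| 30% | 12.143 | 13.8% | 13.626 | 14.5% | 1.85 |

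**Step 4: subject proportions, as the plan reports them.**
- Placebo, all follow-up: 0.01/0.03838 × (1 − 0.60 × e^(−0.18)) = 13.0%. On treatment only: 12.4%, 11.9% and 11.3%.
- At 30% stopping the test arm has 25.2% (all follow-up) and 23.3% (on treatment), from numerical integration of the same model.
- Risk difference at 30% stopping: 25.2 − 13.0 = 12.2 points against 23.3 − 11.3 = 12.0 points.

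**Step 5: a second set of assumptions.** Ignore deaths, spread stopping uniformly over 18 months, and take an 18-month background risk of 5% with an on-drug hazard ratio of 2. The ratio of proportions, all follow-up against on treatment, is 1.90 v 1.95 at 10% stopping, 1.81 v 1.94 at 30% and 1.72 v 1.94 at 50%. The risk difference is 4.51 v 4.52 points at 10% and 3.57 v 3.59 at 50%. The direction is the same, and again the difference hardly moves.

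**Step 6: unequal observation.** Under the planned survival, 15.938/14.095 = 1.13. Take an event at 1% per month that the drug does not affect. It appears in 0.01/0.02380 × (1 − 0.78 × e^(−0.18)) = 14.6% of test patients against 13.0% on placebo. Rates per patient-month remove this difference; subject counts do not.

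**The case against.** **This belongs to the SAP.** Section 8.2 promises detail there, and a post-dose window is commonly set in it. In part this stands: AE start and stop dates are collected, so nothing blocks an on-treatment analysis. But the protocol is not silent. It words a complete two-class rule, and a SAP that follows it would carry the rule over.

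**The drug-related table already deals with it.** A reader might infer that nothing in the plan removes late off-drug events. The documents do not support that. Section 7.3.1 requires a reasonable temporal sequence for the definite, probable and possible categories, so an infection 13 months off drug should fall out of the drug-related summary. This mitigation is real. It rests on case-by-case judgement, though, and leaves the treatment-emergent tables unchanged.

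**The size is an upper bound.** This stands. Section 7.6 says only whenever possible, section 6.8 drops non-compliant patients, and section 6.10.3 withdraws unblinded ones. Sections 5.3, 5.5 and 7.6.1 describe a final-type examination and a visit two weeks after withdrawal. How many patients stop the drug but stay in follow-up cannot be known from the document.

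**The shift is small against the noise.** This also stands. With about 110 per arm and proportions near 13% and 24%, the standard error of the log risk ratio is √(0.76/26.4 + 0.87/14.3) ≈ 0.30. The 95% interval is thus roughly a factor of 1.8 either way. Safety is descriptive, so no confirmatory conclusion changes.

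**Counting everything after first dose has merit.** It keeps the randomised comparison and catches delayed harm. Replacing that table with one cut at drug stop would give unequal and possibly informative exposure if the arms stop at different rates. This argues for adding a table, not replacing one.

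**The SAE form is thin support.** Its three timing boxes apply to SAEs only. They do not show that ordinary AE collection separates the same periods.

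**Conclusion.** The point holds as a minor one. Section 8.2.6 states a treatment-emergent class without an end, and section 7.6 creates the follow-up in which events long after the last dose enter it.

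If 10% to 30% stop by month 18 and every stopper is followed, up to about 4% to 15% of AE observation time is off drug, and a true on-drug rate ratio of 2 reads about 1.95 to 1.85. Stopping concentrated early would enlarge this; incomplete follow-up of stoppers would shrink it. Risk differences change by 0.2 points or less in these scenarios. The unequal observation time, a ratio of about 1.13 if survival is as planned, matters for plain subject counts as well.

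Two stronger readings should be resisted. One is that the safety comparison is seriously compromised: the sizes above and the drug-related table do not bear that out. The other is that section 7.2 already supplies a 14-day window after the last dose: its 14 days run from leaving the study.

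**What to change.** In section 8.2.6, or in the SAP before unblinding:

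1. Keep the table of all adverse events at or after first dose, and label it as all follow-up.
2. Add an on-treatment table, from first dose to last dose plus a window whose length the sponsor states and justifies.
3. Add a post-treatment table by arm for later onsets. Keep the existing worst-case rule for uncertain onset dates.
4. Give rates per patient-month beside the subject counts, with the matching exposure time as denominator.
5. Confirm that the last-dose date is recorded for every patient who stops the drug. Section 7.6.1 asks for the date of premature discontinuation for patients leaving the study. No section was found that requires a last-dose date for those who stop the drug but stay.
6. Reconcile sections 5.3, 5.5 and 7.6.1 with section 7.6 on what follow-up applies after treatment stops. Which rule is intended is for the sponsor to settle.

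The cost is a few lines of text, one or two extra tables and a check of the CRF. The on-treatment table alone could miss delayed effects; the all-follow-up and post-treatment tables still show them.

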### **3 STUDY PURPOSE, TRIAL OBJECTIVES AND ENDPOINTS**

As the efficacy of riluzole to prolong survival in ALS is limited, there is an urgent need to identify other compounds and to evaluate their potential in clinical studies. The pharmacological profile of pioglitazone suggests that this compound may be effective in slowing down the neurodegenerative process observed in ALS and it is therefore important to study this drug in ALS patients. As a significant percentage of patients with ALS will receive riluzole, the study population will consist of patients stabilised on standard riluzole therapy at time of inclusion. After completing this study, patients may have the option to participate in another planned, longer, safety study with pioglitazone.

This study will evaluate the efficacy, safety and tolerability of pioglitazone (45 mg/day) versus placebo in patients with ALS receiving standard, approved therapy (riluzole, 50 mg bid). Mortality defined exclusively as death represents the primary endpoint. Secondary efficacy endpoints will include incidence of tracheotomy or non-invasive ventilation (NIV), ALS Functional Rating Scale (ALSFRS-R; the revised version including the respiratory parameters) and measurement of quality of life using the Euroqol EQ-5D. Assessment of clinical tolerability and safety will be performed by comparison of findings on physical examination, adverse events incidence, and clinical laboratory values across treatment groups.

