## 8 STATISTICS

### 8.1 *Sample size and power considerations*

In four previous ALS trials in which the principal investigator was involved, the rate of loss to follow up was less than 1 % (Exonhit/Pentoxifyllin, ONO2506, 5000 mg Vitamin E trial, TCH346-Novartis-Trial). We expect to repeat this low rate, since ALS is a life threatening disease and the centres involved are experienced in the clinical care for the patients.

The study will be conducted using a two-stage group sequential test design within the  $\Delta$ -class of critical values according to Wang and Tsatis. The planned information rates are 0.5 and 1. These information rates fix the weights for combining the p-values using the weighted inverse normal method. The critical values of the group sequential test design were calculated for the standardised (cumulative) test statistic for the design with boundary shape parameter  $\Delta = 0.0$ , i.e. O'Brien/Fleming type design. For one-sided

$\alpha = 0.025$  and the information rates given above the resulting boundary p-values are given by  $p_1 = 0.00258$  and  $p_2 = 0.02400$  with corresponding critical values 2.797 and 1.977, respectively.

For one-sided  $\alpha = 0.025$  and 18-month survival rates of 60% in the standard group and 78% in the test group (hazard ratio = 0.486), the statistical power is 80% if the log-rank test is performed after observation of a total of 31 deaths at the first stage and after 61 deaths (accumulated number) at the second (final) stage (formula of Schoenfeld, ADDPLAN® version 3.1.2, ADDPLAN GmbH, Germany).

Assuming an accrual time of 6 months and a follow-up time of 15 months (21 months observation time) a total of 198 subjects (99 subjects per treatment group, without drop-outs) is expected to yield the necessary number of deaths if the accrual rate is constant (conservative estimation). Under these assumptions, the time points of analyses are expected to be 11.1 months observation time (interim analysis) and 21 months observation time (final analysis).

Thus, considering a drop-out rate of 10%, it is planned to enrol a total of 220 patients.

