## 8.2 Statistical methods

A Statistical Analysis Plan describing all details of the analyses to be performed will be prepared by the study statistician and approved by the sponsor prior to the start of statistical analysis. The recommendations of the ICH E9 Note for Guidance on Statistical Principles for Clinical Trials (CPMP/ICH/363/96, 1998) will be taken into account.

The primary endpoint will be subjected to a confirmatory analysis. All secondary and safety parameters will be evaluated and reported descriptively.

All individual data as well as results of statistical analyses – whether explicitly discussed in the following sections or not – will be presented in individual subject data listings and statistical summary tables.

Continuous variables will be summarised using the following standard descriptive summary statistics: number of observations, arithmetic mean, standard deviation, minimum, lower quartile, median, upper quartile, maximum. In addition, geometric mean and coefficient of variation derived from log-normally distributed data will be calculated for serum concentrations. Categorical data will be described using absolute and relative frequencies.

A more detailed elaboration of the principal statistical features stated in this protocol will be provided in the statistical analysis plan, which will be finalized prior to unblinding of the database. The statistical analysis plan will take into account any amendment to the study protocol.

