### 8.2.5 Efficacy evaluation

The primary objective of the study is to demonstrate the superiority of the test treatment compared to the standard treatment in terms of survival.

The study will be conducted according to a two-stage group sequential test design with possible sample size adaptation after the planned interim analysis. The overall type-I-error rate is set at  $\alpha = 0.025$  (one-sided).

The following null hypothesis  $H_0$  will be tested against the alternative hypothesis  $H_A$  ( $\alpha = 0.025$ , one-sided):

$$H_0: \lambda_2 / \lambda_1 \geq 1$$

$$H_A: \lambda_2 / \lambda_1 < 1$$

where  $\lambda_2 / \lambda_1$  is the hazard ratio,  $\lambda_1$  denotes the hazard in the standard group and  $\lambda_2$  in the test group. The hazard ratio is assumed to be constant across time.

The null hypothesis will be tested using the log-rank test.

The first interim analysis will be conducted after observation of a total of 31 deaths. The null hypothesis will be rejected at the first interim analysis if the calculated test statistic exceeds the critical value 2.797. In this case, the study may be stopped. If the null hypothesis will not be rejected, the study may be continued until the pre-specified number of 61 deaths (accumulated number of deaths) or a recalculated number of deaths based on the effect size estimation of the first interim analysis were observed.

Data from all subjects will be considered when calculating the second stage log-rank test statistic. At the final (second) analysis, the null hypothesis will be rejected if the calculated inverse normal test statistic exceeds the critical value 1.977.

This procedure preserves the overall (experiment-wise) type I error rate of  $\alpha = 0.025$  in a strong sense.

For estimating the treatment effect, the hazard ratio and the corresponding two-sided 95% repeated confidence interval will be provided.

All other group comparisons are hypothesis generating in nature, i.e., p-values resulting from these statistical tests will be interpreted in the exploratory sense.

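### Section 8.2.6 names only subject counts for adverse events, so for non-fatal events the planned survival difference is mixed into the comparison of arms; patient-time rates beside the counts would separate the two

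*Protocol*

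**What the plan says.** Protocol section 8.2.6 (Safety evaluation) classifies adverse events as pre-treatment or treatment-emergent. It analyses them by seriousness, severity, outcome and causality, and then states the measure: "All analyses will report frequency counts of subjects by MedDRA SOC and preferred term". Section 8.2 adds that "Categorical data will be described using absolute and relative frequencies", so any percentage has subjects as its denominator. Neither section mentions patient-time, exposure-adjusted rates or a time-to-event analysis of adverse events.

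Section 3 says that safety and tolerability are assessed by comparing physical findings, "adverse events incidence, and clinical laboratory values across treatment groups".

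Section 8.1 sizes the trial on "18-month survival rates of 60% in the standard group and 78% in the test group".

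Three further places decide how long a patient is under observation:

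- Section 7.6: patients who stop the drug are to be followed for the study duration whenever possible.
- Section 7.2: follow-up of adverse events ends 14 days after a patient leaves the study.
- Section 7.1.2: an event that results in death is a serious adverse event.

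**The concern.** The calendar window for adverse events is the same in both arms. The time patients spend alive in it is not, if the survival difference that the trial is powered to detect exists. Because patients who stop the drug remain in follow-up where possible, death is the main planned reason for unequal observation.

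A count of subjects with an event then reflects both how often the event arises and how long patients live. For a non-fatal event that is unrelated to dying, such as many cases of oedema or raised liver enzymes (both expected events in section 2.3), two consequences follow. If pioglitazone prolongs survival, it will appear somewhat less well tolerated than its event rate implies. If it shortens survival, its non-fatal signals will be somewhat diluted. A reader of the count tables cannot tell a difference in event rate from a difference in survival.

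**Working it through.** **1. Reproduce the plan's own figures (section 8.1).**

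- Hazard ratio = ln(0.78)/ln(0.60) = 0.486, as stated.
- Schoenfeld events, one-sided 0.025, 80% power, 1:1: 4 × (1.960 + 0.842)² / (ln 0.486)² gives 61 after rounding up. The two-stage design with critical values 2.797 and 1.977 needs 60.9 events and has 80.1% power at 61.
- With 6 months of uniform accrual and analysis at 21 months, 198 subjects give 61.3 expected deaths. The 31st death falls at about 11.2 months (stated: 11.1). Also, 198/0.90 = 220.

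The exponential model used below is therefore consistent with the plan's own calculation.

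**2. Time under observation.** Monthly death hazard λ = −ln S(18)/18:

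- standard: 0.5108/18 = 0.02838
- test: 0.2485/18 = 0.01380

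Mean observed time over 18 months = (1 − S(18))/λ:

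- standard: 0.40/0.02838 = 14.1 months
- test: 0.22/0.01380 = 15.9 months

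The ratio is 0.884 (1.13 the other way), or about 129 versus 146 patient-years per 110 patients. Test over standard, it stays near 1.13 with 10% drop-out in both arms and at the 21-month analysis. At the 11.1-month interim the times are 7.20 and 7.65 months, a ratio of 1.06. The 14-day tail is left out.

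**3. Effect on subject counts.** Let a non-fatal event have the same constant hazard μ in both arms, independent of death. The share of subjects affected by 18 months is μ/(μ+λ) × [1 − exp(−18(μ+λ))]. The documents give no adverse event incidences, so the standard-group value is an assumption and is varied:

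| Standard | Test | Ratio |
|---|---|---|
| 10% | 11.3% | 1.13 |
| 20% | 22.5% | 1.12 |
| 30% | 33.6% | 1.12 |
| 50% | 55.4% | 1.11 |
| 70% | 76.4% | 1.09 |
| 90% | 94.5% | 1.05 |

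The largest gap in this range is about 6 percentage points. Conversely, equal counts would correspond to a true test-to-standard rate ratio of 0.88 at 10% incidence and 0.85 at 50%.

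**4. What a patient-time rate gives.** Mean time to first event, death or month 18 is [1 − exp(−18(μ+λ))]/(μ+λ). In the 10% row (μ = 0.00754) this is 13.26 months (standard) and 14.95 months (test). The rates are 0.100/13.26 and 0.1127/14.95, both 0.754 per 100 patient-months, so the ratio is 1.00.

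**5. Opposite direction.** If the drug raised the death hazard by 50% (an assumption, not a figure from the protocol), its mean observed time would be 12.6 months against 14.1, a ratio of 0.89.

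**6. Tables that include deaths.** Expected deaths by 18 months are 110 × 0.40 = 44.0 and 110 × 0.22 = 24.2. With a non-fatal serious event incidence of 20% in the standard group (assumption), subjects with any serious event including death are 55% versus 42%. Here the arm with more deaths looks worse.

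**The case against.** A reader might infer that the arm with more deaths will look better tolerated overall, or that a drug that increased mortality would have its harm hidden. The documents do not support either reading. Death is a serious adverse event (section 7.1.2) and an outcome category (section 7.1.4), and serious events are analysed by outcome (section 8.2.6). Death is also the primary endpoint, and a committee with access to unblinded data meets every three months (section 10.2.2). Events that cluster shortly before death would also count against the arm with more deaths.

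A reader might also infer that the counts are wrong and that a competing-risk curve would correct them. Neither follows. With equal calendar windows and near-complete follow-up (section 8.1 expects loss below 1%), subjects with an event divided by subjects treated already estimates the cumulative incidence with death as competing event. The formula in step 3 is that function, so such a curve would show the same 1.13. The count answers a legitimate question: what share of patients experienced the event. The rate answers a different one. Choosing between them is a choice of estimand.

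Three more objections carry weight. Safety is descriptive. The effect is small against sampling error: at 10% versus 11.3% it is 11 versus 12.4 patients per 110, while the standard error of the difference is √(0.10×0.90/110 + 0.113×0.887/110), about 4.2 points. It also needs the full design effect and vanishes if survival is equal. Finally, section 8.2.6 does not bar further measures, and the analysis plan announced in section 8.2, which is not at hand, may add them.

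What remains is that the protocol does state a measure, applies it to all adverse event analyses, and that measure alone cannot separate event rate from survival in a trial planned around a survival difference.

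**Conclusion.** The point holds in a limited form, as a cheap improvement to a stated method. Under the plan's survival assumption the test group has about 13% more time under observation. For non-fatal events with equal monthly rates, subject counts would show a ratio of up to about 1.13 (1.05 for very common events), and dilution in the other direction if survival were shorter on the drug. The conclusion does not extend to tables that include deaths.

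It rests on exponential survival within 18 months, the full design hazard ratio of 0.486, a constant event hazard that is unrelated to nearness to death, and illustrative incidences that the protocol does not give.

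**What to change.** In section 8.2.6, keep the subject counts and add beside them exposure-adjusted incidence rates for treatment-emergent, drug-related and serious adverse events, with fatal and non-fatal serious events shown separately. Define the rate as subjects with a first event per 100 patient-months, counting time from first dose to first event, death or end of adverse event collection, and give the rate ratio with a 95% confidence interval. Name the end of collection explicitly: section 8.2.6 gives a start for treatment-emergent events but no end, while section 7.2 gives 14 days after leaving the study. A competing-risk curve is not needed for this purpose.

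The cost is a few extra tables. No new data are needed: event start dates (section 7.2), date of death (section 5.2) and date of premature discontinuation (section 7.6.1) are already recorded, and the treatment-emergent classification already relies on the time of first dose. The downside is that a single rate assumes a roughly constant hazard and is only approximate for events that cluster early, which is a further reason to keep the counts.
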